## Abstract

Hirschsprung's disease (HD) and anorectal malformations (ARM) are congenital colorectal conditions requiring lifelong multidisciplinary care, yet no prospective, longitudinal registry exists for affected children in Canada. We describe the protocol for the COCOE Registry, the first prospective cohort of paediatric patients with HD and ARM at the Colorectal Centre of Excellence (COCOE), Montreal Children's Hospital, McGill University Health Centre, Montréal, Québec, Canada. The registry enrolls children aged 0–17 years with a documented diagnosis of HD or ARM on a continuous basis, with follow-up until age 18. Clinical data are abstracted from a standardised multidisciplinary assessment form and entered into REDCap. Patient-reported outcomes are collected using six validated instruments spanning disease-specific quality of life, continence, general well-being, family functioning, parental adjustment, and bowel management experience. Statistical analyses will include descriptive summaries, group comparisons, survival analyses, and multivariable logistic regression to identify factors associated with key outcomes, reported in accordance with STROBE guidelines. Research ethics approval has been granted by the McGill University Health Centre Research Ethics Board (MUHC REB No. 2026–10997). This study is registered with ClinicalTrials.gov (NCT07603232). The COCOE Registry will generate longitudinal data to improve clinical follow-up, inform healthcare planning, support equitable transitions to adult care, and enable participation in international multicentre research.

## Introduction

Colorectal disorders, particularly Hirschsprung's disease (HD) and anorectal malformations (ARM), represent significant challenges in paediatric healthcare, with lifelong implications for affected children and their families [1–4]. HD is a congenital condition characterised by the absence of ganglion cells in the distal colon, leading to functional intestinal obstruction [1]. In Ontario, Canada, the incidence of HD has been estimated at 2.05 per 10,000 live births [1]. ARM, which encompasses a spectrum of congenital anomalies affecting the anorectal region and frequently associated organ systems, occurs at approximately 1 in 2,162 births in Alberta, with a notable male prevalence (1.7:1) [3,4]. Both conditions require early, often complex, surgical intervention and are associated with lifelong impacts on quality of life, growth, and development.

The management of paediatric colorectal disorders has advanced significantly with the development of specialised multidisciplinary centres, such as the Montreal Children's Hospital's Colorectal Centre of Excellence (COCOE).^8^ This centre is the first of its kind in Québec. Despite advances, children with these disorders often face ongoing challenges, including multiple surgeries, bowel management programmes, and psycho-social support needs. Long-term follow-up is critical, as many patients experience complications such as faecal incontinence, enterocolitis, and issues related to transition from paediatric to adult care [5–7]. For families, these challenges translate into substantial emotional and financial strain, particularly as patients age out of paediatric services [8–10].

Internationally, the importance of systematic data collection has been recognised through the establishment of prospective registries and research consortia. The European Anorectal Malformation Network (ARM-Net) [11,12] and the Paediatric Colorectal and Pelvic Learning Consortium (PCPLC) [13] are leading examples. The PCPLC registry has enabled robust, multicentre research: Rice-Townsend et al [14] found that only 24% of patients with ARM achieved full bowel control across over 500 patients, and Kastenberg et al. [15] demonstrated that rates of postoperative enterocolitis remain high regardless of surgical timing.

Canada has yet to establish a prospective paediatric colorectal registry. Such a registry would allow tracking of long-term outcomes and quality of life, inform continuity of care across the paediatric-to-adult transition, support healthcare planning and resource allocation, and enable participation in international collaborative research [6,11]. We therefore propose the COCOE Registry: a prospective, longitudinal registry of paediatric patients with colorectal disease attending the Montreal Children's Hospital.

## Objectives

The objectives of the COCOE Registry are: 1) to establish the first prospective registry of paediatric patients with HD and ARM in Canada; 2) to collect and analyse longitudinal data on incidence, clinical outcomes, and treatments; 3) to collect patient-reported outcomes on well-being, quality of life, and familial stress and functioning; 4) to improve understanding of regional variations in care and outcomes; and 5) to identify factors contributing to loss to follow-up.

## Methods and analysis

### Study design

This study follows a longitudinal, prospective observational design. The registry has no anticipated completion date; patients are recruited on a continuous basis and followed until they reach 18 years of age. Fig 1 summarises the registry workflow, from identification of eligible patients through consent and baseline data capture to the schedule of longitudinal follow-up assessments and the definitions applied at censoring.

**Fig 1 pone.0356813.g001:**
[figure not shown]
COCOE Registry workflow. Identification of eligible patients, consent and assent, baseline and annual data capture, patient-reported outcome administration schedule, and censoring definitions.

### Study population and setting

Eligible paediatric patients (aged 0–17 years) with documented diagnoses of HD or ARM are invited to participate at the COCOE clinic, Montreal Children's Hospital. Prospective patients are identified through weekly reviews of colorectal clinic schedules.

Although HD and ARM are embryologically distinct conditions with different surgical approaches and long-term outcome profiles, both require lifelong multidisciplinary follow-up and are managed by the same specialist team at COCOE. Enrolling both conditions within a single registry infrastructure reflects this shared clinical pathway and the impracticality of maintaining two separate registries at a single centre. To respect these clinical and methodological distinctions, primary and multivariable analyses will be conducted separately for each disease cohort rather than pooled, with disease-specific instruments and predictors as detailed in the Statistical Analysis section.

### Catchment and representativeness

The Montreal Children’s Hospital is one of two paediatric tertiary care centres in Québec and receives colorectal referrals from across the province, including from Nunavik and the Cree territory of James Bay, as well as selected complex referrals from other provinces. The registry therefore captures a substantial proportion, but not the entirety, of the incident paediatric HD and ARM population in Québec. To quantify representativeness rather than assert it, the age, sex, diagnosis and severity distribution of enrolled participants will be compared at each annual analysis against two external benchmarks: (i) expected provincial case counts, derived by applying published Canadian incidence estimates for HD (2.05 per 10,000 live births [1]) and ARM (approximately 1 in 2,162 births [3,4]) to Québec live-birth denominators; and (ii) the published case-mix of the ARM-Net and PCPLC registries [11,13]. Aggregate, non-identifying information on patients who are approached but decline enrollment (age band, diagnosis, and referral region) will also be recorded so that a non-participation comparison can be reported. Any material divergence, for example under-representation of remote communities or of the most severe Krickenbeck categories, will be reported explicitly alongside registry outputs and taken into account when interpreting external validity.

### Eligibility criteria

Inclusion and Exclusion Criteria are described in Table 1.

**Table 1 pone.0356813.t001:** Inclusion and exclusion criteria.

Inclusion criteria	Exclusion criteria
Aged 0–17 years	Aged 18 years or older
Documented diagnosis of HD or ARM	No diagnosis of HD or ARM
Patients and/or their caregivers or authorised representatives must be able to provide informed consent	Unable to provide consent

### Outcome measures

The primary outcome and its definition are described in detail below. Pre-specified secondary outcomes are presented in Table 2 below, each with its definition, instrument or data source, timing of ascertainment, and analytic role.

**Table 2 pone.0356813.t002:** Pre-specified primary and secondary outcomes.

Outcome	Definition	Instrument / Data Source	Timing of Ascertainment	Priority	Analytic Role
**Time to fecal continence**	First clinic visit (confirmed at subsequent visit) at which the participant meets social continence threshold: BCS criteria (ARM) or BFS ≥ 17 (HD), from date of definitive repair	BCS (ARM) [16] or BFS (HD) [17], parent/caregiver proxy to age 11; self-report from age 12	Annual visits from age 3	**PRIMARY**	Kaplan–Meier estimation; Cox proportional hazards regression; Fine-Gray model for competing risks; landmark analyses at ages 5 and 10
HD-associated enterocolitis (HAEC)	≥1 physician-confirmed episode meeting Ruttenstock criteria requiring medical treatment	Clinical record review; REDCap adverse event log	Each annual visit; first episode date recorded	Secondary 1	Cox regression / Fine-Gray competing risks; descriptive incidence rate
Reoperation rate	Any unplanned surgical return to the operating room following index repair	Operative report review; REDCap surgical procedure log	Cumulative from index repair; each annual visit	Secondary 2	Cox regression / Fine-Gray competing risks; cumulative incidence curve
Disease-specific quality of life	HAQL total score and subscale scores (age-appropriate version)	HAQL questionnaire, self- or proxy-report [18]	Ages 6, 10, and 14 years	Secondary 3	Linear mixed-effects model (repeated measures); descriptive means by group
Transition readiness	Transition Readiness Assessment Questionnaire	TRAQ [19], self-report	Ages 14 and 17 years	Secondary 4	Linear mixed-effects model; descriptive score trajectory
Loss to follow-up (LTFU)	No clinic encounter, survey, or successful contact for ≥18 months while under age 18 and not yet transitioned	REDCap contact log; clinic attendance record	Flagged at 18-month mark; reviewed at each annual analysis	Secondary 5	Logistic regression (ever-lost vs retained); descriptive LTFU rate

The primary outcome is time to achievement of fecal continence from the date of definitive surgical repair, analysed as a time-to-event outcome. For participants with ARM, continence is assessed using the Baylor Continence Scale (BCS) [16], with social continence defined as no soiling episodes in the preceding 4 weeks per published BCS criteria, completed by the parent or caregiver proxy up to age 11 and by self-report from age 12. For participants with HD, continence is assessed using the Bowel Function Score (BFS) [17], with social continence defined as a BFS score ≥ 17, administered to the parent or caregiver proxy up to age 11 and by self-report from age 12. Both instruments are administered at every annual clinic visit beginning at age 3 years. The earliest clinically meaningful assessment for continence is age 3, consistent with normal developmental milestones for voluntary bowel control. Participants will be censored at age 18, death, transition to adult care, or loss to follow-up, whichever occurs first.

Pre-specified secondary outcomes, listed in priority order, are: (1) Hirschsprung-associated enterocolitis (HAEC), defined as at least one physician-confirmed episode meeting the Ruttenstock diagnostic criteria and requiring medical treatment, assessed at each annual visit [20]; (2) reoperation rate, defined as any unplanned surgical return to the operating room following index repair, assessed cumulatively; (3) disease-specific quality of life, measured using the HAQL [18] at ages 6, 10, and 14 years using age-appropriate versions; (4) transition readiness, assessed at ages 14 and 17 years using the validated Transition Readiness Assessment Questionnaire (TRAQ) [19], and (5) loss to follow-up rate, defined operationally in the Loss to Follow-Up section. Each secondary outcome will be reported descriptively and, where the events-per-variable threshold is met (see Sample Size section), included as an endpoint in pre-specified multivariable analyses with the analytic role specified in the Statistical Analysis section.

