### Study timeline and milestones

The registry opened to enrollment on 3 ^rd^ November 2025 and enrollment is ongoing. Formal analyses have yet to be conducted at the time of publication. Below is outlined the Projected Milestones and Study Timeline.

Projected milestones and Study Timeline are as follows:

**Year 1:** incident enrollment fully operational and backlog enrollment at least 25% complete;

**Year 2:** first annual data quality audit completed and first descriptive summary manuscript submitted;

**Year 3:** first interim analysis of the primary outcome conducted for participants who have reached age 5, if the EPV threshold is met;

**Year 4 and 5:** comprehensive registry report including all pre-specified multivariable analyses submitted for publication.

Milestone dates will be updated in subsequent protocol versions as the registry matures. As the study is a longitudinal prospective study, intermittent analyses of the data will be conducted throughout the study duration as is outlined in the Projected Milestones above.

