### Participant recruitment and consent

Written informed consent is obtained from parents or legally authorised representatives at enrollment. Age-appropriate assent is sought from all participants with developing decision-making capacity, consistent with TCPS2 Article 4.2 [23] and MUHC REB guidelines: verbal or picture-assisted assent is used for children aged approximately 7–12 years, and written assent is obtained from adolescents aged 13–17 years, consistent with the age of capacity for research participation under the Québec Civil Code [24]. Assent is documented in REDCap alongside the consent record.

Verbal consent is obtained where written consent is not feasible (e.g., telephone or virtual visits, or when translation is required) and is documented [23], with audio recording where permitted. Participation is entirely voluntary and has no bearing on the care received at Montreal Children's Hospital.

All registry data are de-identified: each participant is assigned a unique registry identifier, and names do not appear on any data collection forms. A master linking log is maintained separately on a password-protected encrypted drive accessible only to the PI. Data are not anonymised in the irreversible sense,  re-linkage to the participant remains possible during active follow-up for clinical and re-contact purposes. Full anonymisation, meaning permanent removal of all re-identification keys, will be applied only upon permanent withdrawal or at study closure.

When a participant turns 18 years of age, active data collection ceases. Data already collected will be retained in de-identified form pursuant to Section 12 of the Act Respecting the Protection of Personal Information in the Private Sector (Québec Law 25, as amended by Bill 64 [25]), which permits continued use of de-identified data for research purposes without renewed consent, subject to ongoing REB oversight (MUHC REB No. 2026–10997).

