### Loss to Follow-Up

A participant will be considered lost to follow-up if there has been no clinic encounter, completed survey, or successful contact (by telephone, email, or mail) for 18 or more consecutive months in a participant aged under 18 years who has not yet transitioned to adult care or withdrawn from the registry.

When a participant misses a scheduled visit without prior notification, the research assistant will initiate a standardised re-contact sequence: (1) two phone call attempts within 2 weeks; (2) email or written letter within 4 weeks, if contact information is on file; and (3) two further phone call attempts at 3 months. If no successful contact is made after this full sequence, the participant will be flagged as lost to follow-up in REDCap with the date of last confirmed contact recorded. All contact attempts and outcomes will be logged prospectively.

Rates and timing will be reported descriptively at each annual analysis. In survival and longitudinal analyses, the loss will be treated as censoring at the date of last confirmed contact. The potential impact of informative (non-random) censoring will be examined using inverse probability weighting (IPW) as a sensitivity analysis [26,27]. Factors independently associated with the loss will be examined using logistic regression (ever-lost vs retained) as a secondary analysis, with candidate predictors pre-specified to include: diagnosis type, age at enrollment, sex, aganglionosis length or ARM Krickenbeck category, area-level deprivation quintile, and distance from COCOE.

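### If Table 2's confirmation rule is applied, children without a confirmed continence event stay at risk past the last visit that could count, so early continence estimates are too low

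*Protocol article*

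**What the plan says.** In Outcome measures, the primary-outcome row of Table 2 gives the event as "First clinic visit (confirmed at subsequent visit) at which the participant meets social continence threshold", with time running from definitive repair. Assessment is yearly: "Both instruments are administered at every annual clinic visit beginning at age 3 years". The analyses listed in that row are "Kaplan–Meier estimation; Cox proportional hazards regression; Fine-Gray model for competing risks; landmark analyses at ages 5 and 10".

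The text below the table sets the end of follow-up: "Participants will be censored at age 18, death, transition to adult care, or loss to follow-up, whichever occurs first". The Loss to Follow-Up section adds that "the loss will be treated as censoring at the date of last confirmed contact". Under Participant recruitment and consent, "When a participant turns 18 years of age, active data collection ceases".

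The same narrative defines the outcome without confirmation: "The primary outcome is time to achievement of fecal continence from the date of definitive surgical repair, analysed as a time-to-event outcome". Objective 3 of the Statistical analysis section does not mention confirmation either.

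Enrolment is continuous. The timeline places the "first interim analysis of the primary outcome conducted for participants who have reached age 5" in Year 3, if the events-per-variable threshold is met, and the full multivariable report in Years 4 and 5.

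**The concern.** Under Table 2, whether a child has an event at a given visit depends on a visit that comes afterwards. A child with K assessments and no confirmed event could have had an event at only K − 1 of them. The stated censoring points nevertheless keep that child in the denominator at the K-th assessment and on to age 18, transition or last contact. At an interim cut the same applies up to the cut, a date that the article implies but does not state. Children with a confirmed event are not affected, because they leave the risk set at their first positive visit.

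At each visit the denominator therefore includes children who cannot supply an event. The Kaplan-Meier continence curve is pulled down, and so are the age-5 and age-10 proportions for children with no later visit yet. If a predictor is related to length of follow-up, the dilution differs between its levels and distorts the hazard ratio. Area-level deprivation is exposed to this: it is a predictor in both Cox models, a candidate predictor of loss to follow-up and an auxiliary predictor of non-response. The planned inverse probability weighting does not remove the problem, which arises even when censoring is purely administrative.

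**Working it through.** **The plan's own figure.** The Sample size section projects 30–35% continence among 480–680 enrolees. 480 × 0.30 = 144 (stated 145) and 680 × 0.35 = 238 (stated 240). Divided by 10, these give 14.4 and 23.8 covariates (stated 14–24). The figures reproduce. They make no allowance for confirmation.

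**General form.** Let h be the probability of a first positive, later confirmed, at a given visit among children still at risk. Under the rule as written, the hazard estimated at that visit is

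h × (share of at-risk children who have a later visit).

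The share is below 1 whenever some children at risk have no later visit. That fixes the direction of the bias.

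**Illustration at a 5-year cut.** Assumptions that are not in the documents: entry uniform over 5 years, annual visits, no dropout, all children assessable and not continent at entry, continence sustained once reached, clock from entry. Follow-up F is then uniform on 0–5 years. The share at visit t is P(F ≥ t+1)/P(F ≥ t):

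- t = 1: (3/5)/(4/5) = 3/4
- t = 2: (2/5)/(3/5) = 2/3
- t = 3: (1/5)/(2/5) = 1/2

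The 3-year estimate is 1 − (1 − 3h/4)(1 − 2h/3)(1 − h/2). The true value is 1 − (1 − h)³. Two values of h are used: 1 − 0.70^(1/5) = 0.0689, which matches the plan's 30% over five annual visits, and an assumed 0.10.

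| h per visit | Year | As written | True |
|---|---|---|---|
| 0.0689 | 1 | 5.2% | 6.9% |
| 0.0689 | 2 | 9.5% | 13.3% |
| 0.0689 | 3 | 12.6% | 19.3% |
| 0.10 | 1 | 7.5% | 10.0% |
| 0.10 | 2 | 13.7% | 19.0% |
| 0.10 | 3 | 18.0% | 27.1% |

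At 3 years the relative shortfall is about one third: (19.3 − 12.6)/19.3 = 35% and (27.1 − 18.0)/27.1 = 34%. Simulation agrees (12.6–12.7% and 18.1%). With 10% annual dropout and h = 0.0689, the simulated 3-year figure as written is 11.4%.

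**What removes the bias.**

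- Censoring at the last completed visit does not. A child is at risk at visit t exactly when F ≥ t, so the shares above are unchanged.
- Censoring at the last-but-one visit does. A child is at risk at visit t only when F ≥ t+1, the share becomes 1, and the estimate is again 1 − (1 − h)³. Simulation gives 19.1% and about 27.2%.
- Dating at the confirming visit does too, one year later on the time axis.

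**Age-5 landmark, children with no visit after age 5.** Visits at 3, 4 and 5 give three chances, of which two can be confirmed. The reading is 1 − (1 − p)^(2/3), so a true 24%, 30% or 39% reads 16.7%, 21.2% or 28.1%.

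**Complete follow-up to 18.** Visits at 3 to 17 give 15 chances, of which 14 can be confirmed. The reading is 1 − (1 − p)^(14/15), so 30% reads 28.3% and 39% reads 37.0%.

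**Hazard ratio.** With equal true hazards (10% per visit) and assumed annual loss of 5% in one group and 20% in the other, simulation gives a hazard ratio of 0.84–0.86 for the higher-loss group as written. It is 0.99–1.00 with last-but-one censoring. The loss rates have no source in the documents.

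**The case against.** The strongest reply is that the article is condensed. Fig 1 is said to show the censoring definitions and is not available here, and the handling of a positive still awaiting confirmation is commonly left to an analysis plan. The written censoring list is also incomplete, since it names no administrative cut. This means one cannot say that the plan has no rule for such children. It does not remove the point: the text itself states the event date and the censoring points, these give a biased estimator together, and the conventional refinement of censoring at the last visit leaves the bias as it was. If Fig 1 does hold a rule, the text and Table 2 still need to match it.

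A second reply is that the detailed definition in the narrative has no confirmation step. This stands as a condition: if the narrative governs, this bias does not arise.

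A third is that the figures are not estimates of the protocol's own quantity. The protocol's clock starts at repair, incident cases may enter well before age 3, the rates are assumed, and Table 2 does not fix 12 months between the first and the confirming visit. This also stands. The figures show scale only.

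Three stronger readings are tempting and are not supported. A reader might infer that the whole age-5 interim estimate is 28–30% too low. That loss applies only to children with no visit after age 5, and the interim also includes older children who may already have confirming visits. A reader might infer a false deprivation effect of known size, but the documents give no loss rates by deprivation, and multivariable Cox waits for the events-per-variable threshold in each cohort. A reader might also infer that the final long-term curves are seriously wrong, but with follow-up to 18 the loss is under 2 to about 2 percentage points.

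**Conclusion.** The point holds on the condition that Table 2's confirmation requirement is applied. Children without a confirmed event then contribute at-risk time in which no event can be counted, and continence is underestimated. The direction needs only that some children at risk at a visit have no later one, which continuous enrolment ensures at every interim cut. The size depends on the assumptions shown: about one third too low at 3 years on a 5-year cut, and small once follow-up to 18 is complete. It matters because the scheduled Year 3 and Year 4–5 analyses fall where the bias is greatest. Hazard ratios can also be distorted by unequal follow-up, by an amount that the documents do not allow one to fix.

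**What to change.** First reconcile Table 2 with the narrative definition and Objective 3 on whether confirmation is required. If it is, choose one rule and state it in Table 2 and in the censoring sentence below it:

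- date the event at the confirming visit; or
- keep the first-visit date and end at-risk time, for every child without a confirmed event, at the last-but-one completed BCS or BFS assessment.

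Apply the same rule to the age-5 and age-10 proportions, and report at each analysis how many positives await confirmation.

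The change takes a few sentences and no new data, and the article says that no formal analysis has yet been done. Confirmation dating moves recorded times one visit later. Last-but-one censoring drops between one and two visit intervals for an unconfirmed child with at least two assessments, and a child with only one assessment contributes nothing. In the 5-year illustration, mean usable follow-up before allowing for events falls from 2.5 years to (0 + 0 + 1 + 2 + 3)/5 = 1.2 years, a loss of 1.3 years per child.

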## Statistical analysis

Analyses are pre-specified by objective as follows.

**Objective 1:** Incidence and clinical outcomes. Descriptive summaries of diagnosis, surgical procedures, and complication rates will be reported using means (SD) or medians (IQR) for continuous variables and frequencies (%) for categorical variables [39]. Time-to-event outcomes (e.g., first HAEC episode, reoperation) will be analysed using Cox proportional hazards regression. Where competing risks are present (e.g., death or transition to adult care prior to the event of interest), the Fine-Gray subdistribution hazard model will be applied [40]. Candidate predictors for each time-to-event model are pre-specified as: diagnosis type, Krickenbeck category or aganglionosis length, age at index repair, sex, syndromic status, and area-level deprivation quintile.

**Objective 2:** Patient-reported outcomes. Longitudinal PROM/PREM data collected across multiple clinic visits will be analysed using linear mixed-effects models (for continuous scores) or generalised estimating equations (GEE; for binary or count outcomes), with an unstructured or autoregressive covariance structure selected by the Akaike Information Criterion [41]. Cross-sectional group comparisons at a single timepoint will use chi-square or Fisher's exact tests (categorical) and independent-samples t-tests or Mann-Whitney U tests (continuous), as appropriate.

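### HAEC is modelled as time to the first episode with no anchor at index repair, so episodes before repair can be the counted event in a model that has age at repair as a predictor

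*Protocol article*

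**What the plan says.** All references are to the protocol article.

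- **Definition.** Table 2 under Outcome measures gives HAEC as "≥1 physician-confirmed episode meeting Ruttenstock criteria requiring medical treatment". The text below the table repeats it: "defined as at least one physician-confirmed episode meeting the Ruttenstock diagnostic criteria and requiring medical treatment, assessed at each annual visit". Neither mentions repair.
- **Source and date.** The Table 2 source is "Clinical record review; REDCap adverse event log" and the timing entry is "Each annual visit; first episode date recorded".
- **Analysis.** Under Objective 1 of Statistical analysis: "Time-to-event outcomes (e.g., first HAEC episode, reoperation) will be analysed using Cox proportional hazards regression". A Fine-Gray model is added where competing risks exist. The candidate predictors for every such model include "age at index repair, sex, syndromic status, and area-level deprivation quintile". No time origin is stated for HAEC.
- **Contrast.** The primary outcome, time to continence, runs from definitive repair. Reoperation is counted cumulatively from index repair.
- **Who is enrolled.** The Sample size section has a stream of newly diagnosed children, at least 5 per month across both diseases. Surgical procedures are recorded with their dates.

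**The concern.** Enterocolitis in Hirschsprung's disease can occur before or after repair, and the endpoint does not separate the two. A pre-repair episode cannot have been caused by the age at which repair later took place, yet it would count as an event in a model that has that age as a predictor. The episode may itself have changed when repair was done. The coefficient would then describe a mixture: the relation of repair age to later HAEC, the longer time at risk before a later repair, and any effect of HAEC on the repair date.

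HAEC is first in the protocol's priority order of secondary outcomes. The limitations section also foresees comparison with other registries' data, and the Introduction cites a postoperative enterocolitis result from one of them. An endpoint that mixes episodes before and after repair would not be comparable with a postoperative rate.

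**Working it through.** **No figure to reproduce.** The protocol states no HAEC rate, event count or power. The check is a reading of the definition under each possible clock, followed by an illustration.

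**Step 1: the definition under each clock.** Take a hypothetical child with a first episode at 2 weeks and repair at 3 months (about 13 weeks).

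- *Clock from birth or diagnosis.* The event is at 2 weeks of age. The predictor takes its value about 11 weeks later, so the model conditions on the future.
- *Clock from repair.* The event time is 2 − 13 = −11 weeks, which Cox regression cannot use. The child must be dropped, counted at time zero, or given a later postoperative episode whose date the protocol does not specify.

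No origin makes the endpoint and the predictor fit together as written.

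**Step 2: illustration under a true null.** None of these assumptions comes from the documents.

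- Age at repair A = 0.02 + gamma(shape 1.2, scale 0.4) years, capped at 5; simulated median 0.37 years.
- Constant post-repair hazard of 0.10 per year, unrelated to A, with 5 years of follow-up after repair.
- Constant pre-repair hazard h of 0.05 to 0.60 per year; no effect of HAEC on repair timing.
- 60,000 simulated children per setting.

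Two quantities have closed forms, ignoring the cap:

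- Share with a pre-repair episode: p = 1 − exp(−0.02h) × (1 + 0.4h)^(−1.2). For h = 0.60: 1 − 0.988 × 0.7725 = 0.237.
- Share of counted first events that precede repair: p / [p + (1 − p)q], with q = 1 − exp(−0.10 × 5) = 0.3935. For h = 0.60: 0.237 / (0.237 + 0.300) = 0.44.

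The hazard ratios (HR) per year of age at repair come from Cox fits to the simulated data.

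| Pre-repair hazard per year | 0.05 | 0.15 | 0.30 | 0.60 |
|---|---|---|---|---|
| Children with a pre-repair episode | 2% | 7% | 13% | 24% |
| Counted first events that precede repair | 6% | 16% | 28% | 44% |
| HR, first-ever HAEC, clock from birth | 0.90 | 1.11 | 1.38 | 1.77 |
| HR, clock from repair, pre-repair events at time zero | 1.15 | 1.34 | 1.61 | 1.94 |
| HR, first post-repair HAEC, clock from repair | 1.02 | 0.98 | 1.01 | 1.01 |

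The true value is 1 throughout. On the birth clock the HR is below 1 when the pre-repair hazard (0.05) is lower than the post-repair hazard (0.10), and above 1 when it is higher.

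**Step 3: sensitivity to the set-up.** Other null runs had repair planned at 0.5 to 6 months, 10% or 20% of children with pre-repair HAEC, and the clock from birth. Their HRs are per 3 months of repair age, so they are not on the scale of the table.

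- No delay of repair after an early episode: about 0.90 if pre-repair HAEC is unrelated to planned repair age, and 1.15 to 1.38 if it accrues at a constant hazard.
- An early episode delays repair by 1 to 3 months: 1.2 to 2.1 in one set of runs and up to 3.6 in another.

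**Step 4: postoperative dates.** In the Step 2 runs, 2%, 7%, 13% and 24% of children with a postoperative episode had an earlier pre-repair one. These shares merely return the pre-repair shares put in, because the two processes were simulated as independent. They illustrate who is affected and are not evidence of how many.

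**The case against.** The strongest reply is that much of this is detail a statistical analysis plan would supply: the time origin, the handling of events before it, and recurrent events. Reoperation cannot precede repair, so its anchor proves little about what was intended for HAEC. Adjusted models run only once 10 events per variable are reached within the disease cohort, and the protocol warns that this may come late for Hirschsprung's disease. Age at repair is one of several candidate predictors, not a named exposure.

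These points limit the consequences but do not remove the problem. Table 2 is presented as fixing each outcome's definition, source, timing and analytic role, and the predictor is pre-specified. The combination fails under any origin (Step 1). If later dates are not abstracted, an analysis plan cannot supply them.

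Four stronger readings are tempting, and the documents do not support them:

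- *Later episodes are undated and cannot be analysed.* The protocol specifies the first date but does not say that only this date is kept. The adverse event log may hold others, and the data dictionary is not shown.
- *The Introduction makes postoperative HAEC by surgical timing this registry's question.* The sentence that "rates of postoperative enterocolitis remain high regardless of surgical timing" reports another registry's result. The Objectives do not ask that question.
- *The simulated hazard ratios estimate the bias.* They rest on assumed rates, delays and clocks.
- *The incidence rate is wrong unless it counts recurrences.* A first-event rate is legitimate; total episodes per person-year is a different estimand.

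**Conclusion.** The point holds in a limited form. As written, the HAEC endpoint admits pre-repair episodes, and the model relates them to a repair age fixed only afterwards. That the age-at-repair coefficient then mixes in events preceding repair follows from the definition, provided some enrolled children have HAEC before repair; enrolment of newly diagnosed children and chart review make that possible.

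The size and direction of the bias cannot be stated. They depend on pre-repair HAEC rates and on any effect of HAEC on repair timing, and the documents give neither. The null illustrations run from slightly below 1 to well above 1. Restricting the endpoint to post-repair episodes timed from repair brought the estimate back to 0.98 to 1.02.

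The second consequence is conditional: a child whose first episode is pre-repair has no specified date for a first postoperative episode, unless the log holds it. This is a secondary outcome and the primary analysis is untouched. Enrolment opened on 3 November 2025, so the collection rule should be settled early.

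**What to change.** In Table 2, the outcome text and Objective 1 of the Statistical analysis section:

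1. Define the modelled endpoint as first HAEC after index repair, timed from index repair, with delayed entry for children enrolled after repair.
2. Among HAEC models, use age at index repair as a predictor only in that one.
3. Record pre-repair HAEC (yes/no, with date) as a baseline variable and report it separately.
4. Require the adverse event log to hold at least the first pre-repair and the first post-repair episode dates.

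Reporting all postoperative episodes per person-year is optional.

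The cost is one extra date field, some wording and fewer counted events. In the Step 2 setting the counted share falls from p + (1 − p)q to q: from 0.408 to 0.394 at the lowest pre-repair hazard (about 4% fewer) and from 0.537 to 0.394 at the highest (about 27% fewer). The events-per-variable threshold for HAEC may therefore be reached somewhat later. Surgical dates are already collected, and HAEC is already reviewed at each annual visit.
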